### Sample size

As our primary outcome variable is the total mean score on a self-report questionnaire - Mental Health Continuum - Short Form (MHC-SF) [49] - which measures mental well-being using Likert scaling, we consider this outcome as a continuous variable. Normality of the distribution will be checked after data collection using optimal scaling or scatter plotting. When the assumption of normality is violated, resampling methods will be used to transform the data into a normal distribution.

An accurate sample size estimation is challenging since no other studies have been performed with a comparative experimental design and intervention within the same population. Former studies evaluating mentoring programs show small to medium effect sizes [50–53], whereas studies investigating psychological, educational and behavioral treatments show larger mean effect sizes [54]. Effect sizes of life coaching performed in a nonclinical sample show medium to large effect sizes [55]. Given the foregoing, we expect a small to medium improvement of mental well-being in the FNC condition compared to TAU. We consider this a realistic and clinically meaningful effect. Our first power calculations (conducted with G*Power) indicated that 150 participants are needed (75 per arm) to detect a small-to-medium effect size (Cohen’s *f* = .20), given an alpha of 0.05 (two-tailed) and a power of 0.80. Since this power calculation did not account for the repeated measures design of the study, more modern power calculations were performed (conducted with STATA) to calculate the required sample size. To detect a small-to-medium effect size (Cohen’s *f* = 0.20) in a pairwise comparison of pre-post change between two active treatment arms, with a power of 0.80 and a within-person correlation coefficient of 0.50, 68 participants are needed in this study (34 per arm). We expect 30% of the participants as early drop-outs of the study [56], therefore a total of 105 participants will be included in the study.

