### Primary outcome measure

#### Mental wellbeing

The Dutch version of the Mental Health Continuum - Short Form (MHC-SF) will be administered to measure the current psychological, emotional and social wellbeing during the last month [49, 74]. The MHC-SF is a 14-item self-report questionnaire that consists of a 5-point Likert scale. The psychometric features of the MHC-SF are good. There is evidence for a high internal and moderate test-retest reliability and good convergent and discriminant validity [74]. The mean score of the psychological, emotional and social wellbeing scales - the (positive) mental wellbeing score – will be the primary outcome of this study. Assessment of the primary outcome variable will be conducted at baseline and 3, 6, 9, 12 and 18 months after baseline. The mean difference of the mental wellbeing score between groups over time - from baseline to assessment at 12 months - will be chosen as the main outcome measure of this study. Table 1 provides an overview of all instruments and the corresponding time of assessment.

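### The 68 participants (34 per arm) given for 80% power do not follow from the stated inputs: for the pre-post comparison described, power is about 37% to 47%

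*Protocol article*

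**What the plan says.** The sample-size section of the protocol article gives two calculations for the same effect size.

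- **First calculation (G*Power).** For f = 0.20, "given an alpha of 0.05 (two-tailed) and a power of 0.80", it "indicated that 150 participants are needed (75 per arm").
- **Reason for replacing it.** "Since this power calculation did not account for the repeated measures design of the study", a second calculation was run in STATA.
- **Second calculation.** The target is again f = 0.20, this time "in a pairwise comparison of pre-post change between two active treatment arms". The result printed for this comparison reads: "with a power of 0.80 and a within-person correlation coefficient of 0.50, 68 participants are needed in this study (34 per arm"). Alpha is not repeated.
- **Drop-out.** "We expect 30% of the participants as early drop-outs of the study [56], therefore a total of 105 participants will be included".

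Under Mental wellbeing, the main outcome measure is fixed as "The mean difference of the mental wellbeing score between groups over time - from baseline to assessment at 12 months". The Statistical analysis section plans a mixed model that uses all assessments, corrects for baseline, and tests the group effect and the group-by-time interaction. It does not say whether time is linear or categorical.

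**The concern.** The second calculation keeps the effect size and power of the first and cuts the requirement from 150 to 68, by more than half. The enrolment target rests on 68. The section describes one pre and one post measurement with correlation 0.50. At that correlation a change score has the same variance as a single score, so taking change saves nothing. Baseline adjustment saves a quarter, which cannot produce a reduction to 34 per arm.

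What is at stake is how the result will be read. The article calls the target effect realistic and clinically meaningful and says the trial has 80% power for it. If power for the 12-month contrast is nearer 40% to 50%, a null result would be taken as evidence against the coaching when the trial could easily have missed the effect.

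**Working it through.** **Inputs.** From the sample-size section: f = 0.20, so d = 2f = 0.40 for two equal arms; r = 0.50; power 0.80; 34 per arm; 30% drop-out; 105 randomised. Alpha 0.05 two-sided is printed for the first calculation and assumed for the second. Allocation is 1:1 (Randomization and procedure). The score SD is set to 1. Unless marked otherwise, powers use the noncentral t.

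**Step 1. The comparison described.**

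- Change score: variance 2(1 − r) = 2 × 0.5 = 1.00, SD 1.00.
- Baseline-adjusted: variance 1 − r² = 1 − 0.25 = 0.75, SD 0.866.
- Normal approximation: n per arm = 2(1.96 + 0.8416)² × variance / d², with (1.96 + 0.8416)² = 7.849.
  - Change: 2 × 7.849 × 1.00 / 0.16 = 98.1 (100 by noncentral t).
  - Adjusted: 2 × 7.849 × 0.75 / 0.16 = 73.6 (75 by noncentral t).

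| Per arm | Change score | Baseline-adjusted |
|---|---|---|
| 34 | 0.37 | 0.47 |
| about 37 (105 × 0.70 / 2 = 36.75) | 0.40 | 0.50 |
| 52.5 (105, no drop-out) | 0.53 | 0.65 |

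At 34 per arm, 80% power needs d = 0.69 (f = 0.34) or d = 0.60 (f = 0.30). At about 37 per arm it needs d = 0.66 (f = 0.33) or d = 0.57 (f = 0.29). The Statistical analysis section calls f = 0.25 moderate and 0.40 large, so all four lie above moderate. With d = 0.40, 34 per arm would need r of about 0.83 (change) or 0.81 (adjusted).

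**Step 2. Can the printed 34 be reproduced?**

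- *One-sided 5%:* power at 34 per arm is 0.49 (change) or 0.59 (adjusted). No.
- *f as a group-by-time interaction effect, two measurements:* the noncentrality is f² × N × 2 / (1 − r) = 0.16N. N = 52 gives 0.81 and N = 68 gives 0.90. For change scores the noncentrality is N × d² / 4, so d = 0.80. This neither returns 68 nor fits a small-to-medium effect.
- *Baseline-adjusted mean of five follow-ups (3, 6, 9, 12, 18 months), all correlations 0.50, constant 0.40 SD effect:* variance (1 + 4 × 0.5)/5 − 0.25 = 0.35; n = 2 × 7.849 × 0.35 / 0.16 = 34.3 per arm. Power at 34 is 0.80 (normal) or 0.78 (t). Close.
- *Linear group-by-time slope over 0, 3, 6, 9, 12, 18 months, random intercept, no random slope, 0.40 SD difference at 12 months:* mean time 8; squared deviations 64 + 25 + 4 + 1 + 16 + 100 = 210; residual variance 1 − r = 0.5; slope 0.40/12 = 0.0333. n = 2 × 7.849 × (0.5/210) / 0.0333² = 33.6, so 34 per arm. A match.

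**Step 3. How far the two multi-visit readings carry.**

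- The slope model implies 0.40 × 18/12 = 0.60 SD at 18 months. Without that visit the squared deviations sum to 36 + 9 + 0 + 9 + 36 = 90 and n = 2 × 7.849 × (0.5/90) / 0.0333² = 78.5 per arm.
- The five-visit mean needs the full effect from month 3, yet the section on forensic network coaching gives the first three to six months to motivation and alliance. As an illustration only (the values are assumed, not in the article), effects of 0.1, 0.2, 0.3, 0.4 and 0.4 SD average 0.28 SD and give power 0.49 at 34 per arm.
- With time categorical, the baseline-adjusted 12-month contrast at 34 per arm has power of about 0.48 (normal approximation), essentially the Step 1 value.

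**Cross-check on the first figure.** A plain two-group comparison at d = 0.40 needs 100 per arm. The printed 75 per arm equals the baseline-adjusted requirement at r = 0.50 (power 0.80). So 150 appears already to use the pre-post correlation, and introducing that correlation cannot explain the fall to 68.

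**The case against.** The strongest reply is that the trial is not planned as a two-timepoint comparison. The second calculation was made to reflect repeated measures, and the planned analysis is an all-visit mixed model with a group-by-time interaction. A linear-time version on the trial's own schedule, with the stated f and r and alpha carried over, gives 34 per arm and expresses a 0.40 SD difference at 12 months. The definition of f is not given, and a condensed article may leave the software settings to the full protocol.

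Much of this stands. A reader might infer that 68 is an arithmetic slip, that no model yields it, or that the planned analysis has only 37% to 47% power. The documents do not support any of these. Two multi-visit models come close to 34 or return it, and the coding of time is not stated. Depending on that coding, power at 34 per arm runs from about 0.48 to 0.80.

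The reply does not rescue the text. The section does describe what was powered, and it describes a pairwise pre-post comparison. Nothing in the article states a linear trajectory, the absence of a random slope, or a difference growing to 0.60 SD at 18 months. The linear reading also depends on a visit six months after the declared 12-month endpoint.

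**Conclusion.** The point holds as a mismatch between a printed number and its printed inputs. For f = 0.20, r = 0.50 and a between-arm comparison of pre-post change, 34 per arm gives about 37% power (change score) or 47% (baseline-adjusted), against a stated 80%. The requirement is about 100 or 75 per arm. Inflating to 105 does not restore 80% for that comparison, even with no drop-out.

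This rests on d = 2f in units of the score SD and on two-sided alpha 0.05 carried over from the first calculation. Which model produced 68 cannot be settled from the article. In either case the section needs correcting: in its number if a two-timepoint comparison was meant, or in its description if a multi-visit model was run.

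**What to change.** Rewrite the second calculation in one of two ways.

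1. **Keep the description and correct the power.** For the baseline-to-12-month contrast, state that with 105 randomised and 30% drop-out, power for f = 0.20 is about 40% (change score) or 50% (baseline-adjusted), and that the effect detectable with 80% power is about d = 0.66 (f = 0.33) or d = 0.57 (f = 0.29).
2. **Keep 68 and correct the description.** If it came from a multi-visit model, replace the pre-post wording with that model: the visits used, the coding of time, the random effects, the definition of f, alpha, and the constant-effect or linear-effect assumption. Make the primary analysis match it. Do not attach the 80% to a two-timepoint or categorical-time 12-month comparison.

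Either way, report the 12-month difference with its confidence interval so that a null result is not read as no effect. The cost is a rewritten paragraph and, under the first option, a less favourable stated power. Under the second, the primary model must also be specified to match. Neither needs more participants.

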### Procedure

#### Recruitment and consent

Patients will be recruited at all outpatient sites of Inforsa Forensic Mental Health Care, a department of Arkin Mental Health Care, a large mental health care institute in Amsterdam, the Netherlands. Recruitment is planned for 2 years. Patients will be screened for eligibility by a clinician and researcher during treatment. Researchers will inform and stimulate clinicians to refer patients by participating in team meetings, spreading information flyers, reminding clinicians, spreading newsletters and monthly presentations. When eligibility is assumed, the clinician will introduce the study to the patient to check whether the patient is interested in participating. After a patient expresses interest, more extensive screening between the clinician and researcher will take place.

Subsequently, the first recruitment appointment will be scheduled with eligible patients who agreed to be approached by a researcher. During the first appointment the patient will be screened for eligibility by a researcher. Furthermore, patients’ motivation for participation will be assessed. All eligible patients receive a written study information letter. The content of the study information letter will also be explained by a researcher. Depending on the preferences of the patient, the second appointment for the screening interview, informed consent and baseline assessment will be planned. The second appointment will take place at least a week after the first face-to-face appointment so enough time for consideration is provided. In addition, the researcher asks whether the patient agrees to be approached by a research assistant by phone, in order to check agreement with participation, to answer questions and to plan appointments for follow-up assessment.

During the second appointment, informed consent will be signed by all patients. After informed consent, baseline assessment will take place in which all in- and exclusion criteria are checked again by a researcher. If necessary - to decrease the burden for participants - baseline assessment will be divided into multiple appointments. The baseline assessment should preferably be completed within 1 month after informed consent.

#### Randomization and procedure

Independent research assistants and research associates - not familiar with the patient or responsible for any kind of mental health care - of the research department of Inforsa are involved in the recruitment procedure, randomization, data collection and data management of this study. Randomization will be performed at an individual level, stratified by forensic outpatient care site. We aim to carry out randomisation after completion of (the first half of) the baseline assessment. A computer-generated block randomization schedule provided by Castor Electronic Data Capture (EDC) is used. The allocation ratio will be 1:1 to ensure that an equal number of patients will be allocated to either TAU or FNC. Researchers will not have access to the randomization schedule and will be blind to block size and order. Blinding for treatment after randomization is not possible, as the content of treatment will be clear to both patients and therapists. Blinding researchers is not feasible due to different assessments of the conditions and required coordinating activities - referring patients to FNC and monitoring - of researchers during the FNC intervention.

The experimental intervention starts preferably within 2 months after completion of the baseline assessment and ends 12 months after baseline assessment. During the intervention, patients in both FNC and TAU condition will be assessed at 3, 6 and 9 months after baseline assessment. At the end of treatment (12 months) and follow-up (18 months) additional questionnaires will be administered. Figure 1 provides an overview of the trial design. Two supplemental measures, the Work Alliance Questionnaire (WAV-12) and a qualitative interview, will only be assessed in the experimental group. Table 1 provides an overview of all instruments and the corresponding time of assessment.

**Table 1 Tab1:** Overview of outcome measures, instruments and time of assessment from baseline in months

Outcome	Concept	Instrument	baseline 0	3	6	9	end 12	follow-up 18	36
**Primary**	Mental wellbeing	MHC-SF	•	•	•	•	•	•	
**Secondary**	Psychiatric functioning^a^	HoNOS	•	•	•	•	•	•	
	Criminal recidivism	SRD	•				•	•	
		IPOL					•		•
		JDS					•		•
	Substance abuse	MATE 2.1	•	•	•	•	•	•	
	Quality of life	MANSA	•	•	•	•	•	•	
	Social network	NGI-method	•				•	•	
	Social support	SSL	•				•	•	
	Loneliness	Loneliness Scale	•				•	•	
	Self-sufficiency	SSM-D	•	•	•	•	•	•	
**Mediators / Moderators**	Diagnostic classifications	DSM-IV-TR/5	•						
		MINI-plus	•						
	Life trauma events	CTQ-SF	•						
	Attachment style	ASQ	•				•		
	Demographic characteristics	Self-developed	•				•	•	
	Working alliance^b^	WAQ-12		•	•	•	•		
	Intellectual disabilities	SCIL	•						
	Cognitive distortions	HIT-Q	•						
	Program integrity^c^	Self-developed					•		
**Other variables**	Qualitative interview of experiences ^b^	Self-developed					•		

^a^ this outcome measure will be scored by a researcher based on interviews, questionnaires and observations during assessments and information from patient files

^b^ this interview will be assessed for participants and forensic network coaches in the experimental group

^c^ this outcome measure will only be assessed for forensic network coaches in the experimental group

Forensic network coaches will receive an e-mail with a request to fill in one online questionnaire at 3, 6, 9 and 12 months after baseline assessment. In addition, after termination of the experimental intervention at 12 months, forensic network coaches will be interviewed face-to-face to measure program integrity and coaching experiences. Audio recordings will be made of every qualitative interview with both patients and coaches. Besides, researchers fill in questionnaires about patients in both conditions, at 3, 6, 9, 12 and 18 months after baseline, based on observations during assessment and information from the electronic patient file. Registered criminal recidivism data at 12 and 36 months after baseline will be requested by a researcher after termination of the study.

All assessments with patients - interviews and questionnaires - will be conducted face-to-face, using both paper and pencil and online questionnaires using Castor EDC. The research assistant will help participants with possible problems and difficulties during assessments. The data collection process will be carefully monitored. All patients and forensic network coaches will be frequently motivated by research associates to complete the assessments. If necessary, patients and coaches will be reminded via the phone or e-mail. If necessary, the assessments can also be completed by phone. All patients will be compensated with a gift card of €10,- after each assessment at 3, 6, 9 and 12 months. After completion of the last assessment, 18 months after baseline, patients receive a gift card of €25,-.

All collected data from interviews and questionnaires will be entered and stored online and in the onsite database. To promote data quality researchers will be trained in the study protocol and adequate administration of assessments. Weekly supervision sessions and team training meetings will be used to evaluate assessments. All data will be checked on missing data or specific errors or contradictions in data. Most of the time assessments will be filled in by patients on paper, therefore double data entry procedures will be performed to prevent defaults in data entry. Data entry and encoding by research associates will be consequently checked by a second associate. Besides, independent random data checks will be conducted on entry and encoding defaults.

Participants may withdraw from the study or experimental intervention for any reason at any time. Discontinuation of treatment as usual or early discontinuation of the experimental intervention is not a reason for withdrawal from the study. In case of early discontinuation of the intervention patients will be motivated for participation during the following research assessments.

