### Participants

This study is conducted at the outpatient care site of Inforsa Forensic Mental Health Care, specialist in forensic psychiatric care for (young) adults, located in Amsterdam. Inforsa consists of three different forensic outpatient care sites: 1) forensic flexible assertive community treatment (forensic FACT) for adults, 2) forensic FACT for youth and young adolescents, and 3) forensic outpatient clinic. The overall patient population of Inforsa is characterized by complex addiction, psychiatric and personality disorders in combination with delinquent behavior. The type of crimes committed by patients are diverse, most common offences are violence or theft. Treatment is a mandatory part of a conditional sentence, for 87% of the patients. The majority of the patients (69%) suffers from psychiatric or personality disorders in combination with addiction - double diagnoses. On top of that, at least 11% of the patients suffers from intellectual disabilities - triple diagnosis. Most patients have social problems such as housing problems, work problems and financial problems.

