### Interventions

#### Treatment as usual (TAU)

The vast majority of potential participants receives forensic FACT which can include specific therapeutic interventions such as social work, psychotherapy (e.g. CBT, EMDR) and pharmacotherapy. We will include patients at the forensic outpatient care site not receiving forensic FACT as well if social network-related problems are present and social participation is limited. All forensic outpatient care sites include psychotherapies and treatment models that are part of the treatment guidelines for forensic outpatients.

In short, forensic FACT is a widely used treatment model developed for forensic outpatients with severe psychiatric disorders, combined with multiple social problems [19]. The primary goal of forensic FACT is to enhance (mental) wellbeing as well as to reduce the risk of criminal recidivism. Forensic FACT teams consist of different health care professionals such as psychiatrists, nurses specialized in psychiatric problems, psychologists, job coaches and social workers. Treatment is delivered within the community of the patients. In general, individual face-to-face appointments between professionals and patients take place weekly at the institution or at a patients’ home. The intensity of the treatment is customized to the patient’s needs. If necessary, for example in case of (the prevention of) a crisis, the frequency of appointments can be increased and more professionals can be involved. Furthermore, CBT or psychotherapeutic interventions are indicated and performed by psychologists based on the patients’ needs and their individual risk assessment of criminal recidivism. Examples of common interventions are aggression regulation therapy [57], CBT for alcohol- or drug-use disorders [58], community reinforcement approach [59], delict analysis [60] and motivational interviewing [61]. CBT interventions and psychotherapy consist of weekly face-to-face appointments at the participating site. Besides, interventions may also be offered online or blended.

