## Statistical analysis

An intention-to-treat analysis will be included in the data analyses of the primary outcome measure (mental wellbeing) and secondary outcome measures (psychiatric functioning, criminal recidivism, substance abuse, quality of life, social network, social support, loneliness and self-sufficiency). Besides, subgroup analyses will be conducted on the protocol completers sample. Generalized Linear Mixed Models (GLMM) in Statistical Package for the Social Sciences (SPSS) will be used to model all continuous outcome measures, considering the distributional characteristics of the data. If the normal distribution assumption is violated, resampling methods will be used to transform data into a normal distribution or appropriate non-parametric tests will be used. Generalized Estimating Equations (GEE) will be used to analyze the categorical outcome measures. The main between-group effect (TAU versus FNC) and the interaction effect (group * time) will be analyzed whilst correcting for baseline assessment. Outcome data of all assessments will be included in the analyses to examine the differences in the development in time between both groups. The criminal recidivism data will be analyzed using Survival Analysis and corrected for time at risk. Missing data will be addressed using multiple imputation or statistical techniques that control for missingness-at-random.

To assess the magnitude of treatment effects on the primary outcome and secondary outcomes, Cohen’s *f* effect size will be calculated. Effect sizes of *f* = 0.40 are considered large, effect sizes of *f* = 0.25 are considered moderate and effect sizes of *f* = 0.10 are considered small (Cohen, 1988).

Moderator analyses will be used to examine potential moderators of treatment outcome by adding potential moderators as covariates of factors to the GLMM/GEE analyses. Furthermore, multilevel mediation models will be carried out to examine potential mediators of treatment outcome. At last, appropriate statistical methodology in ATLAS.ti will be used for the analyses of the qualitative data [111].

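### Randomisation is stratified by care site, but the stated outcome models do not name site; if site is prognostic beyond baseline, some precision is forgone

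*Protocol article*

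**What the plan says.** Under Randomization and procedure the protocol article says: "Randomization will be performed at an individual level, stratified by forensic outpatient care site". The method is blocked: "A computer-generated block randomization schedule provided by Castor Electronic Data Capture (EDC) is used". Allocation is 1:1.

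The Participants section gives the number of strata: "Inforsa consists of three different forensic outpatient care sites". These are forensic FACT for adults, forensic FACT for youth, and an outpatient clinic. No site shares are given. The TAU section adds only that "The vast majority of potential participants receives forensic FACT", without splitting adult from youth teams.

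The Statistical analysis section gives the terms of the outcome models: "The main between-group effect (TAU versus FNC) and the interaction effect (group * time) will be analyzed whilst correcting for baseline assessment". Recidivism is to be analysed by survival methods corrected for time at risk. Site is named in neither place, and it is not among the potential mediators and moderators in Table 1. The section does not say that its list of covariates is complete.

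**The concern.** Balancing the arms within site makes the true variance of the treatment contrast smaller than under simple randomisation, to the extent that site predicts the outcome. A model that includes site takes that gain. A model that leaves it out puts the between-site variation back into the residual. Its standard error is then larger than the true sampling variation, its confidence intervals are too wide and its test rejects less often than the nominal 5%.

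Site could be prognostic here because the strata differ by age group and by treatment model. An analyst who followed the published text to the letter would fit models that ignore the one factor on which randomisation was stratified. At stake is precision, in a trial planned on 34 evaluable participants per arm. Fixing the covariate set before the results are known is a further reason to name the factor.

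**Working it through.** **Inputs from the article.** Three strata, blocked 1:1 allocation, 34 evaluable per arm, 30% dropout, 105 in total. Alpha and power are stated for the first sample size calculation, "given an alpha of 0.05 (two-tailed) and a power of 0.80"; the two-sided 5% level is assumed to carry over to the second.

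**Assumed.** R², the share of outcome variance left after baseline that site explains. The article gives no site variance or intraclass correlation, so a range of 0 to 0.20 is shown.

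**The plan's own figure.** The 34 per arm for 80% power is not reproduced from its stated inputs. With f = 0.20 (d = 0.40) and correlation 0.50, the SD of change is √(2(1 − 0.5)) = 1. That gives 99 per arm, and 34 per arm has about 38% power. This is a separate matter. To isolate the effect of site, the treatment effect is set so that 34 per arm has the planned 80%: (1.960 + 0.842) × √(2/34) = 2.802 × 0.2425 = 0.68 residual SD.

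**Formulas** (normal approximation, one post-baseline endpoint, exact balance within site), with k = 1/√(1 − R²):

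- reported SE without site ÷ true SE = k
- type I error without site = 2[1 − Φ(1.960k)]
- power without site = Φ(0.842k)
- power with site = Φ(2.802k − 1.960)

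Example, R² = 0.10: k = 1/√0.90 = 1.054. Type I error is 2[1 − Φ(2.066)] = 3.9%. Power without site is Φ(0.887) = 81.3%; with site it is Φ(0.993) = 84.0%.

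| Assumed R² | SE overstated | Type I error without site | Power without site | Power with site | Points forgone |
|---|---|---|---|---|---|
| 0 | 0% | 5.0% | 80.0% | 80.0% | 0 |
| 0.01 | 0.5% | 4.9% | 80.1% | 80.4% | 0.3 |
| 0.05 | 2.6% | 4.4% | 80.6% | 82.0% | 1.4 |
| 0.10 | 5.4% | 3.9% | 81.3% | 84.0% | 2.7 |
| 0.20 | 11.8% | 2.8% | 82.7% | 88.0% | 5.3 |

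**Simulation check.** 68 participants, assumed site split 70/15/15, blocks of 4, ANCOVA, 6,000 runs per setting. At R² = 0.05, power was 78.9% without site and 80.2% with it, and null rejection 4.5% and 5.0%. At R² = 0.10, power was 78.9% and 81.5%, and null rejection 4.1% and 5.0%. At R² = 0, where site cannot matter, null rejection was 5.7% without site and 5.75% with it. The Monte Carlo standard error near 5% is √(0.05 × 0.95/6000) = 0.28 points, so single entries are approximate.

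**Dropout.** Losses disturb the balance within site and so shrink the discrepancy. With 105 randomised (assumed strata 62/23/20, blocks of 4) and random loss to 74, type I error without site was 4.9%, 4.0% and 3.3% at R² = 0.05, 0.10 and 0.20 (8,000 runs). The exact-balance values are 4.4%, 3.9% and 2.8%.

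**The case against.** The strongest reply is that the article never says baseline is the sole covariate. Its analysis section is short and covers six kinds of analysis, and a full covariate list is commonly left to a longer protocol or analysis plan that is not shown. This stands in part. A reader might infer that site has been ruled out, and the text does not support that. It does name the correction it intends for the outcome models and, separately, for the recidivism analysis, and the stratification factor is in neither.

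Second, the effect is conditional. Baseline wellbeing already absorbs part of any difference between sites, and most candidates receive forensic FACT. If site adds nothing beyond baseline, nothing is lost. This stands, and it is why the table starts at zero.

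Third, a reader might infer that the trial loses planned power or that its result would be biased. Neither follows. The sample size took no credit for site adjustment, so in the table power without site never falls below 80%. The error is conservative and the point estimate stays unbiased in the linear model. The difficulty in reproducing the sample size cannot be used to add weight here.

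Fourth, the check uses a single endpoint in a linear model, not the planned repeated-measures GLMM or GEE. The figures are therefore a guide to size only.

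**Conclusion.** The point holds in a conditional and modest form. The design stratifies by site and the stated analysis does not name it. If site is prognostic beyond baseline, model-based standard errors are somewhat too large and tests conservative. For an assumed R² of 0.01 to 0.10, the overstatement is 0.5% to 5.4% and 0.3 to 2.7 power points are forgone; at 0.20 it is 11.8% and 5.3 points; at zero there is no effect. Dropout of 30% makes these somewhat smaller. They rest on the assumed R², a linear model, and an effect scaled to the planned 80% power.

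It would be tempting to extend the same statement to the recidivism analysis. That was not computed. Survival models respond to omitted covariates differently from linear ones, and the number of events is unknown, so no size is claimed there.

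**What to change.** State in the analysis section that care site (three levels) enters every GLMM and GEE model as a fixed factor, alongside the baseline value of the outcome. The cost is two degrees of freedom per model and no new data, since site is already recorded for randomisation. If a fuller analysis plan already includes it, a cross-reference is enough.

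For the recidivism survival models, say how site will be accounted for, as a covariate or as a stratum, depending on what the number of events per site allows. Small strata with few events can cost information, so this choice should not be assumed to be free.
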